## Abstract

**Background:**

Mobile health (mHealth) interventions can improve health by improving cardiovascular risk factors, but their adoption in care by physicians and patients is untapped. Few mHealth apps have been evaluated in clinical trials, and due to the fast pace of technological development, those previously evaluated are often outdated by the time trial results are available. Given the rapid pace of change in this field, it is not feasible to rigorously evaluate mHealth apps with current methodologies.

**Objective:**

The overall aim of this pilot study was to test the feasibility of using a web research platform called Trial My App to conduct efficient and rigorous web-based randomized controlled trials (RCTs) of mHealth apps relevant to patients with cardiovascular risk factors by evaluating an app that targets hypertension.

**Methods:**

For this study, 200 participants with suboptimally controlled hypertension will be recruited through advertisements in newsletters, media, and the internet, as well as through referrals from their health care providers. Screening, consent, randomization, and collection of patient-important health confidence and self-management ability outcomes will be conducted online through the Trial My App research platform. Participants will be randomized into 2 groups: 100 that will use an mHealth app for tracking hypertension and 100 that will be considered as an educational control. All participants will complete questionnaires at 0, 1, 3 and 6 months after enrolment. A substudy to validate the method of blood pressure readings and the consistency of data entered through Trial My App will be conducted with 40 participants.

**Results:**

The development of the Trial My App web platform has been completed. The creation of survey instruments has been completed in collaboration with our patient partners and advisory board. Recruitment is expected to begin in the first quarter of 2021; data collection and analysis are expected to be completed approximately 1 year after study commencement. Results will be disseminated through conferences and publications. The primary outcomes of this study include the feasibility of conducting an RCT using the Trial My App platform by reporting recruitment, retention, and completion statistics. We will validate app-entered data with a standard 7-day home blood pressure measurement method. Lastly, the pilot, nonblinded RCT will assess the effectiveness of the mHealth app in improving the control of hypertension compared with the control of hypertension in the educational control group.

**Conclusions:**

This study will determine if it is feasible to use the Trial My App web-based platform to evaluate the effectiveness of mHealth apps for patients with cardiovascular risk factors. As more mHealth apps are evaluated in RCTs, patients will be able to select apps that meet their needs and physicians will be able to make evidence-based recommendations to their patients for apps aimed at improving cardiovascular health.

**Trial Registration:**

ClinicalTrials.gov NCT04528654; https://clinicaltrials.gov/ct2/show/NCT04528654

**International Registered Report Identifier (IRRID):**

PRR1-10.2196/26155

## Introduction

Smartphones provide continuous connection to the internet and can run sophisticated software apps. Globally, over 3.5 billion individuals own a smartphone [1]. The delivery of health care interventions via mobile phones is known as mobile health (mHealth). In 2017, 86% of the Canadians surveyed owned a smartphone or tablet and 78% downloaded mHealth and other types of apps to these devices [2]. Of the 66% of Canadians who indicated that they self-track at least one aspect of their health, 40% used electronic devices to do so and 32% reported using at least one mHealth app to monitor their health [2,3]. Other authors have reported that up to 58% of the smartphone users have downloaded an mHealth app [4] and 3.6 billion health apps were projected to be downloaded in 2017 [5]. Since smartphones are used to track health and are often continuously carried by users, mHealth apps allow for frequent data collection and feedback for behaviors that affect health, and interventions can be deployed to many users at a relatively low cost [6].

Health behaviors, including smoking, inactivity, and poor diet, are the major contributors to cardiovascular disease [7]. The American Heart Association has endorsed provider and patient self-management of cardiovascular disease risk factors as an effective form of secondary prevention [8]. Though the field of mHealth is in its infancy, early studies have shown that apps can improve health-related behaviors and reduce cardiovascular risk factors, largely through knowledge translation, by improving adherence to or by uptake of medications and behaviors that are known to be effective [9]. Randomized controlled trials (RCTs) report that apps can help patients lose weight [10-14], quit smoking [15], and increase physical activity [16]. An RCT of lifestyle-focused text messages reduced low-density lipoprotein cholesterol levels, systolic blood pressure, and BMI in patients with coronary heart disease [17], and a systematic review of RCTs of home blood pressure telemonitoring showed reduced systolic and diastolic blood pressure [18,19]. Thus, current data suggest that mHealth interventions can improve health by improving such cardiovascular risk factors, but their adoption in health care by physicians and patients is minimal. The 2014 National Physician Survey of licensed Canadian physicians reported that 83% did not recommend mobile apps to their patients, although 72% of the general practitioners and 53% of the specialists referred patients to websites and 50% used mobile apps such as e-textbooks or calculators in their practices [20]. We recently conducted a needs assessment survey of 113 physicians, which showed that over half of the physicians recommended apps to their patients despite their lack of clinical evidence. Many physicians in the survey indicated that they rely on personal opinions and patient recommendations to support their recommendations of apps despite wanting to choose apps that have a higher level of evidence such as RCTs or expert panel reviews. Our needs assessment also indicated that physicians do not recommend apps because they are not aware of them or do not have time to review their clinical efficacy. Without proper testing and evaluation, gaps in app development, including lack of expert involvement, poor user input validation, lack of evidence base, and poor quality of information, may pose clinical risks and safety harms to consumers [21]. With the growing interest in mHealth to monitor patient health, it is imperative that physicians stay informed and minimize their medical-legal risks by recommending apps with proven efficacy.

Despite this desire for better evidence, only a minority of the mHealth apps available in web-based app stores and commonly downloaded by patients have been evaluated in clinical trials, and due to the fast pace of technological development, those that have been evaluated are often outdated by the time trial results are available. Of the top 100 grossing health and fitness apps, researchers found that none had been formally evaluated in clinical studies [22]. Multiple reviews have highlighted the lack of quality research evidence on the efficacy of apps [9,23-25]. mHealth research has several unique challenges contributing to this problem. Chiefly, technology is rapidly progressing and equally rapid techniques for evaluating such technology are needed. Testing must be cost-efficient, given the limited funding for evaluating mHealth interventions compared with pharmacological interventions or medical devices [9]. These constraints limit the evidence base and the incorporation of apps in patient care.

The rapid proliferation of smartphone technology provides untapped potential to improve the efficient conduct of such research. Using internet-enabled devices to perform research can potentially (1) accelerate large-scale enrolment by contacting and screening potential participants who do not frequently interact with the health system through clinics or hospitals and (2) reduce costs and improve participation by allowing frequent and inexpensive data collection directly from participants. With the rapid development of internet-connected and smartphone-connected consumer devices that can collect biometric data, smartphones also have the potential to collect objective, real-time data directly from patients [26].

## Methods

### Overview

We have developed an innovative research approach using a web-based platform called Trial My App, which is designed to perform efficient trials of apps relevant to patients with cardiovascular risk factors. In our initial phase, we engaged an advisory board of patients to codevelop criteria for app and trial outcome selection, which will be used to support further deployment of Trial My App. The patients used apps for goal setting, decision-making, information sharing, and empowerment in managing their health. From these themes, we derived a series of survey questions to determine if an app was meeting these outcomes, and we included this survey in the pilot trial. Content analysis by the advisory board also indicated that patients considered a number of favorable technical factors when selecting their mobile apps: (1) relevant feedback on progress, (2) security, (3) low cost, (4) customizability, (5) usability, (6) information credibility, (7) multifunctional app integration, and (8) interdevice compatibility. The undesired features were as follows: (1) unreliable technology, (2) distraction, (3) collection of personal information, and (4) learning curve. These criteria were applied to shortlist apps for hypertension, and through discussion with the research team and patient partners, we identified Sphygmo BP as the intervention app for this pilot trial (Multimedia Appendix 1). Sphygmo BP was created in partnership with the University of Alberta to help patients with hypertension to self-manage their blood pressure. The app tracks and averages blood pressure, glucose levels, weight, temperature, respiratory rate, and oxygen saturation. It also includes educational components to facilitate better patient awareness of management strategies for blood pressure and is designed to facilitate patient-physician communication through telemonitoring.

### Objectives

The primary objective of the study is to test the feasibility of conducting an RCT of an mHealth hypertension-tracking app using the Trial My App platform. The secondary objective is to test if the use of the Sphygmo BP app reduces blood pressure in patients with suboptimally controlled hypertension when compared with the use of a website with information on hypertension. It would be valuable for patients and physicians to know whether the use of the app is likely to result in reductions in blood pressure that have been shown to reduce clinical outcomes.

### Study Design

This is a pilot, nonblinded parallel-group RCT, comparing the use of a hypertension app versus an education control in participants with suboptimally controlled hypertension. Outcomes include feasibility, clinical, and patient-important endpoints.

### Eligibility Criteria

The inclusion criteria are as follows: (1) age over 18 years, (2) diagnosis of hypertension, (3) interested in using an app for hypertension management, (4) access to a smartphone with internet connection, and (5) access to a blood pressure monitoring device (in home or community setting, eg, pharmacy). The exclusion criteria are as follows: (1) participant-reported blood pressure within target (target range for patients with diabetes is systolic blood pressure <130 mm Hg and diastolic blood pressure <80 mm Hg; for those without diabetes, target range is systolic blood pressure <140 mm Hg and diastolic blood pressure <90 mm Hg according to Hypertension Canada guidelines [27]) within the 2 weeks prior to enrolment, (2) emergent hypertensive concerns (potential participants with systolic blood pressure ≥180 mm Hg or diastolic blood pressure ≥120 mm Hg will be advised to seek medical attention and will be excluded), (3) current use of a mobile app for hypertension management, (4) living outside of Canada, (5) pregnancy, and (6) unwillingness or inability to give informed consent.

### Recruitment

The primary study site will be the Health Information Research Unit at McMaster University in Hamilton, Ontario. A combination of passive and active recruitment strategies will be used. A variety of recruitment materials will be distributed by a research assistant throughout the community and outpatient or specialty clinic waiting rooms. These materials include videos, papers, and web-based posters/postcards, emails, as well as posts advertising on social media. Social media recruitment on Facebook, Twitter, and Google Network will consist of general posts and targeted ads using Facebook Ads Manager. Partner newsletters and websites include Hamilton Academy of Medicine, McMaster Institute for Research on Aging, McMaster Okanagan Charter, and RSearch. We will also engage clinicians and their administrative staff within the McMaster Department of Medicine, Hamilton Health Sciences outpatient clinics, Queen Square Family Health, and other community, primary, and specialty clinics in Ontario to identify potential participants and invite them to register with Trial My App to determine if they want to participate in the trial. Snowball sampling through participants and personal networks may also be used. Interested candidates will be provided a link or a quick response code to access the website within the marketing materials. They could also contact our research assistant through a dedicated Trial My App email account if they prefer the initial contact by email or phone.

All trial stages, including screening, consent, randomization, and collection of clinical and patient-important outcomes data, will be performed virtually using the Trial My App platform. This phase includes a substudy to validate the web-based collection of patient data. Ethics approval of the substudy will be sought separately. Participants will be asked to register on the Trial My App site with an email and a password. The informed consent form is in Multimedia Appendix 2. Once they have electronically consented to using the web app, they will complete a user profile questionnaire and be screened for participation in the pilot trial in a subsequent survey. Multimedia Appendix 3 contains all user baseline, screening, and follow-up questionnaires. If participants meet inclusion criteria, they will be asked to electronically consent to take part in the pilot trial and provide data at 0, 1, 3, and 6 months. The participant flow is shown in Figure 1. The diagram of the app flow is shown in Figure 2.

**Figure 1 figure1:**
[figure not shown]
Participant flow diagram. RCT: Randomized controlled trial; mHealth: mobile health.

**Figure 2 figure2:**
[figure not shown]
Trial My App web flow diagram. RCT: randomized controlled trial.

### Sample Size

In the feasibility study, at least 80% of the participants in each group who successfully complete the final questionnaire within 1 year of trial start will be considered as the primary feasibility outcome. To estimate a completion rate of 80% in each group within a margin of error of 8% and with a confidence interval of 95%, we estimated a sample size of at least 100 participants in each group, and 200 participants in total is required. With a sample size of 200 participants in total (ie, 100 per group), we will have 80% power to detect a reduction in blood pressure of 8 mm Hg, which is considered a minimally clinically important difference. Assuming an 18 mm Hg standard deviation in systolic blood pressure, to detect an 8 mm Hg difference between groups with a power of 80% and a type I error of 5%, we would ideally require 81 participants in each arm [28]. Accounting for a 20% dropout rate, we aim to enroll 100 participants in each arm. We recognize that the selected app may not result in such a large difference in the systolic blood pressure, but the calculation is to guide our recruitment targets. If a difference in the blood pressure is found, we will be able to inform patients and physicians that this app may have a major impact on clinical outcomes such as heart attack, stroke, and congestive heart failure. 

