### Data Collection

At 1, 3, and 6 months after enrollment into the RCT, Trial My App will send email reminders with a link to follow-up questionnaires to all participants to assess self-reported blood pressure and several patient-reported outcomes. Completing follow-up will be defined as answering the questionnaire within 7 days of receipt of the questionnaire notification via email. To encourage participation and reduce attrition, participants will receive a Can $10 (US $1=Can $1.27) electronic gift card for each completed assessment and an additional Can $10 gift card if they complete all 4 follow-up assessments.

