**Clinical assessment**		
	Difference in mean change in blood pressure from baseline to 6 months between groups	Statistically significant difference in mean change in systolic blood pressure measurements (defined as *P*<.05 using a Pearson test)
	Proportion of patients at their recommended blood pressure	Blood pressure measurements compared to standard ranges

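### The 80% power for 8 mm Hg rests on an SD worded as that of systolic BP itself, while the outcome is change from baseline and the named tests do not fit it; a baseline-adjusted linear model would bring them into line

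*Protocol article*

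**What the plan says.** **Sample Size.** The blood pressure comparison is sized from a stated spread and target, "Assuming an 18 mm Hg standard deviation in systolic blood pressure, to detect an 8 mm Hg difference between groups", with 80% power and a 5% type I error. The result is "we would ideally require 81 participants in each arm", followed by "Accounting for a 20% dropout rate, we aim to enroll 100 participants in each arm". No SD of change and no correlation between baseline and follow-up readings is given.

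**Table 2, Clinical assessment.** The outcome is "Difference in mean change in blood pressure from baseline to 6 months between groups". Its indicator is a P value below .05 for mean change in systolic BP from a Pearson test. A second blood pressure outcome is the proportion of patients at their recommended level.

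**Statistical Analysis.** Efficacy outcomes are to be compared between groups by logistic regression. No covariate is named or ruled out.

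**Data Collection and Recruitment.** Participants provide data at 0, 1, 3 and 6 months, and the follow-up questionnaires ask for self-reported blood pressure.

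**The concern.** Two things do not line up.

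First, the SD used for sizing is worded as the spread of systolic BP, a level, while the outcome is a change. The two spreads coincide only under a particular relation between the baseline and 6-month readings, which the article does not state. The power sentence therefore carries a hidden assumption.

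Second, the article does name tests for this outcome, and they match neither the power calculation nor each other. A power calculation from an SD and a mean difference presupposes a comparison of two means. Logistic regression needs a binary outcome, and a Pearson test is, as named, a test of correlation or of a contingency table.

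The claimed 80% power for the main efficacy outcome is at stake. Low correlation is possible here: the readings are self-reported, the device may be in a pharmacy, they are six months apart, and the Discussion itself lists measurement error. Feasibility Outcomes also frames the primary goal as completing an adequately powered trial, so the basis of the power claim should be clear.

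**Working it through.** **Inputs from the article:** difference 8 mm Hg; SD 18 mm Hg; power 80%; type I error 5% (taken as two-sided, which reproduces the plan's figure); 1:1 allocation; 100 enrolled per arm with 20% dropout, so 100 × 0.8 = 80 completers per arm.

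**Assumptions:** the baseline to 6-month correlation r; the baseline SD wherever it differs from 18.

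**Step 1: reproduce the plan.** The normal approximation is n = 2 × [18 × (1.960 + 0.842) / 8]² = 79.5, so 80 per arm. With the t distribution, power is 0.798 at 80 and 0.803 at 81 per arm, so 81 is the smallest number reaching 80%. The stated 81 is correct for an SD of 18. Eighty completers is one short of 81, which is of no consequence.

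**Step 2: unadjusted change score, equal SDs of 18 at both visits.** SD of change = 18 × √[2(1 − r)].

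**Step 3: 6-month value adjusted for baseline.** Residual SD = 18 × √(1 − r²), which never exceeds 18.

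Power at 80 per arm for 8 mm Hg (t distribution):

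| r (assumed) | SD of change | Power, change score | Residual SD | Power, adjusted |
|---|---|---|---|---|
| 0 | 25.5 | 0.51 | 18.0 | 0.80 |
| 0.2 | 22.8 | 0.60 | 17.6 | 0.81 |
| 0.3 | 21.3 | 0.66 | 17.2 | 0.83 |
| 0.4 | 19.7 | 0.72 | 16.5 | 0.86 |
| 0.5 | 18.0 | 0.80 | 15.6 | 0.90 |
| 0.6 | 16.1 | 0.88 | 14.4 | 0.94 |
| 0.7 | 13.9 | 0.95 | 12.9 | 0.98 |

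Under equal SDs the change score reaches 80% power at r of about 0.50 with 80 per arm, and at about 0.37 if all 100 per arm are analysed (normal approximation).

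**Step 4: allow for the eligibility limits.** Eligibility Criteria exclude systolic BP of 180 or more and BP within target, which may make the baseline SD smaller than 18. As an illustration, a uniform baseline from 140 to 180 has SD 40/√12 = 11.5, and from 130 to 180 it has SD 50/√12 = 14.4. Let r be the correlation before this restriction, and keep the slope and residual variance it implies, so that the restriction also lowers the observed correlation. Then:

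SD of change = √[18²(1 − r²) + (1 − r)² × SD_baseline²].

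| r (assumed) | Change score, baseline SD 14.4 | Change score, baseline SD 11.5 | Adjusted, either SD |
|---|---|---|---|
| 0.2 | 0.67 | 0.71 | 0.81 |
| 0.3 | 0.71 | 0.75 | 0.83 |
| 0.4 | 0.77 | 0.80 | 0.86 |

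For example, at r = 0.3 and baseline SD 14.4: √[324 × 0.91 + 0.49 × 207.4] = √396.5 = 19.9, power 0.71. The shortfall is smaller than under equal SDs, and adjustment still has the higher power in every row.

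**The case against.** The strongest case against is that nothing in Sample Size is miscalculated. The 81 reproduces, no correlation is given, and nothing in the article shows that r is below 0.5. Above 0.5 a change score exceeds the stated power. All of this stands. A reader might infer that the trial is underpowered, or that the power holds only if r is at least 0.5. The article supports neither: the 0.5 threshold needs equal SDs at the two visits, and the eligibility limits make that doubtful.

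A reader might also infer that the plan rejects baseline adjustment and discards the 1- and 3-month readings. That would be reading silence as a decision. The article names no covariate but excludes none, an adjusted model also estimates a difference in mean change, and such detail is commonly left to an analysis plan, which is not shown here.

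The 18 mm Hg may have been meant as the SD of change. The 80% would then hold for a change score at any r, but the sentence does not say so.

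The Pearson test could be read charitably as the correlation between change and group, which is equivalent to the unadjusted t-test. That is precisely the change-score comparison calculated above, and it would still conflict with the logistic regression.

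Finally, blood pressure is the secondary, pilot objective. The 100 per group is separately justified by the precision of the completion rate (1.96 × √(0.8 × 0.2/100) = 7.8%, within the stated 8%), and the article says the power calculation serves to guide recruitment. This limits the consequence. It does not remove the mismatch, because the article states the outcome, the SD and the tests, and they do not fit together.

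**Conclusion.** The concern holds as a mismatch between the power basis and the stated outcome and tests, not as a wrong sample size. As worded, 18 mm Hg is the SD of a level. On that reading, an unadjusted change score with 80 completers per arm and equal SDs has power from about 0.60 (r = 0.2) to 0.95 (r = 0.7), passing 0.80 at r of about 0.5. With a narrower baseline spread the loss is milder: 0.71 to 0.75 at r = 0.3 for baseline SDs of 14.4 to 11.5. The correlations and baseline SDs are assumptions, so the size of any shortfall is uncertain.

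The direction is firmer. Adjusting for baseline keeps power at about 80% or higher at every r (0.81 to 0.98 for r from 0.2 to 0.7), at the price of one degree of freedom, and it gave more power than the change score in every narrowed-baseline case shown. It is worth correcting before analysis, with consequences limited to the secondary objective.

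**What to change.** 1. In Table 2 and Statistical Analysis, replace the Pearson test and logistic regression for systolic BP with a linear model of 6-month systolic BP on group, adjusted for baseline systolic BP. Logistic regression can stay for the proportion at recommended blood pressure.
2. In Sample Size, state that 18 mm Hg is the SD of the systolic BP level and that the baseline-adjusted analysis maintains the 80% power. If it was meant as the SD of change, say that instead.
3. Optionally, use a repeated-measures model with the 1-, 3- and 6-month readings, so that participants lost before month 6 still contribute. This is a preference, not a correction.

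The cost is wording only. The baseline and follow-up readings are already planned, and the sample size does not change.
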